## Results

### Pilot

In order to validate the protocol and refine the entire intervention process by collecting actionable recommendations for how to execute the various phases, we conducted a pretest pilot from January to April 2018 among 6 pairs of participants (6 grandparents and 6 grandchildren). The validation of the protocol was focused on the process, instruments, and technological setup. We continued the study after the validation, and 59 pairs of participants (59 grandparents and 59 grandchildren) were recruited. Data collection was completed in November 2019.

### Challenges and Lessons Learned

#### Low Recruitment Rate of Study Participants

We recruited study participants at the Mongolian National University of Medical Sciences. We screened approximately 260 students to recruit participants who met the inclusion criteria. Students were excluded because the inclusion criteria “living separately from their grandparents” and “grandparents living in Ulaanbaatar city” were not met. The low rate of recruitment was related to the fact that the number of students who came from the countryside is much higher than that of students who reside in the city. Based on this experience, we recommend extending the recruitment pool to reach young participants who meet the age criteria but are not necessarily affiliated with any university. In addition, disseminating the online recruitment survey is another possible solution to increase recruitment rate.

#### Scheduling Issues in Home Visits

Although older adults were willing to participate in the study, the appointments for home visit (to collect pictures and stories) were in some cases cancelled or postponed because grandparents were sick, had a doctor’s visit, traveled to the countryside, or were celebrating holidays. Therefore, researchers need to consider potential delays in data collection when developing the time frame of the study.

#### Enjoyable But Lengthy Conversation With Grandparents

Older adults were willing to share photos and stories and enjoyed the sessions. Because older adults were eager to share their stories and photos and the interviewers were attentive to this situation and did not rush the interviews, the duration of the conversations was much longer than the 1 hour initially allocated. We recommend researchers account for this aspect when scheduling reminiscence sessions.

#### Managing Preferences While Ensuring Diversity in the Pictures

When selecting the pictures for the study, older adults expressed preferences on certain pictures to share, which affected our diversity criteria for the pictures and stories. To address this situation, we recommend not imposing the choice on the participants but expanding the number of pictures from which to select.

#### Sharing Pictures on Social Media Raised No Privacy Concerns

Grandparents expressed no privacy concerns in sharing the pictures, stating that they knew the pictures were meant to be shared only with their grandchildren. We recommend being transparent about how the pictures will be shared and treated.

#### Managing the Picture and Story Sharing Proved Feasible on Facebook

The setup consisted of a closed group on Facebook accessible only to the grandchildren. This setting was accepted by the participants, and the sharing was carried out without any difficulties. Pictures were shared every week, and grandchildren were interactive using Facebook reactions such as thumbs up or hearts as feedback on the posts. A few of the participants also expressed their gratitude by commenting on the posts.

#### Running the Proposed Study Process Is Feasible

The grandchildren could easily understand and complete the questionnaires. There were no complaints regarding the questionnaire or the set up of the Facebook groups. In addition, some of the grandchildren said that they enjoyed being part of the study because it reminded them about positive memories of their childhood as well as their grandparents. There were no dropouts.

### Alternative Study Designs

We identified two potential issues that led us to propose alternative study designs. The first issue was balancing the intervention and control group (equipoise). The grandchildren who agree to participate in this study will likely do so to experience the intervention. Thus, assigning them to the control group would not fulfill their decision to be involved in this study. To address this potential issue, we propose a crossover design where control and intervention groups would be swapped after the 2-month intervention period so that the control group becomes the intervention group and vice versa. After the crossover, the same intervention process would be applied for another 2 months, allowing all participants to experience the intervention. Incidentally, the second intervention period would serve as a follow-up for the intervention group. The second issue was low rate of recruitment. In case the researchers are unable to randomize 60 pairs of participants at the same time due to low rate of recruitment, a quasiexperimental design would provide flexibility in choosing the control group, allowing those who agree to participate in the study to experience the intervention (to join the intervention group). The potential selection bias in this alternative should be noted, however. May any of the above changes become necessary, amendments to the current version of the protocol will be applied and communicated to the relevant venue.

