## Methods

### Study Design

The study is designed as a randomized controlled trial (RCT) where both the intervention and control group consist of grandparent-grandchildren pairs. In the intervention group, we collect a set of pictures and short stories about the grandparents and share them with the grandchildren’s social network account, one at a time, at regular intervals across a period of 2 months. In the control group, there is no sharing or collecting pictures as the goal is to account for alternative effects.

Figure 1 shows the diagram of the study flow. Restricted randomization will be performed by stratifying gender, initial closeness level of the grandchildren, and age group of the grandparents. This paper reports on a version of the protocol accepted by the Research Ethics Committee at Mongolian National University of Medical Sciences in December 2017 (No. 2017/3-05).

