### Participants

The aim is to recruit 60 grandparent-grandchild pairs, which will be split evenly into intervention and control conditions. The sample size is limited by the specific focus of the intervention and the availability of participants complying with the criteria, but it represents a valid sample for the statistical analyses. A convenience sample will be used in this study to recruit participants. We consider eligible pairs of grandchildren and grandparents meeting the following inclusion criteria.

Grandchildren should be willing to participate in the study and meet the following requirements:

Aged 18 to 30 years: we recruit young adults because this is a transition period to adulthood associated with changes in the level of interactions and relational closeness [13]Be regular users of Facebook: we use Facebook because this is the most common social media among Mongolian young adults [29], and we define regular users as those who check their accounts every 2 to 3 days or more oftenHave infrequent meetings with their grandparent: the proposed intervention is aimed at improving relationships between grandparents and grandchildren who do not have much opportunity to meet and talk. Therefore, we recruit grandchildren who live separately from their grandparents (not in the same apartment or building) and do not meet with their grandparents more than once a week on average

In addition, the grandchildren should have one grandparent willing to participate in the study who meets the following requirements:

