### Recruitment

Grandchildren will be recruited from the public universities in Ulaanbaatar, Mongolia, using online as well as paper-based recruitment surveys. As a first step, we will reach students by introducing the study and its goals at the end of their lectures. Those interested in participating in the study will then stay in the classroom to complete the recruitment survey and sign the consent form. The survey will include filtering questions, reflecting the inclusion criteria for grandchildren, and will ask participants to provide an email or phone number for a follow-up. Students who met our inclusion criteria and who have stated their willingness to invite their grandparents to join in our study will be contacted by the researchers to confirm the interest of their grandparents and organize a phone interview. The list of potential candidates will be managed electronically, with access provided only to the researchers in charge of the recruitment.

As a second step, the researchers will contact the grandparents for a phone interview to confirm their eligibility. At the end of the phone interview, a follow-up visit will be scheduled with the grandparents who met the inclusion criteria. We will recruit study participants and make visits until we have 60 pairs that meet the inclusion criteria and agree to participate.

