### Limitations

There are number of possible limitations to this study. First, unsuccessful recruitment of study participants, which led us to reconsider the study design, can be a limiting factor. However, the issue can be attributed to the specific demographical characteristics of Mongolia, as the most sparsely populated country, and other countries may see better chances at successful recruitments. In addition, we proposed an RCT design to identify the impact of social media in the intergenerational relationship instead of a more robust multiple armed RCT design. Although the latter would have been more effective in identifying other factors influencing the intervention, its application would have required a larger population sample, which would have added further challenges to an already complicated recruitment process. Therefore, we opted for collecting qualitative data at the end of the study (debriefing session) to identify additional factors in the intervention, thus mitigating the risks involved in recruiting a larger sample. Furthermore, the study will be carried out only in the city; therefore, people who live in rural areas are not included. Finally, the recruitment will be implemented by reaching out only to the grandchildren; therefore, the future studies will consider involving grandparents in the recruitment in order to reduce the selection bias.

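### The conditional fallback for slow recruitment gives up randomisation, although slow accrual only calls for randomising pairs as they enrol

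*Protocol article*

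**What the plan says.** The operative design is randomised. Study Design states: "The study is designed as a randomized controlled trial (RCT) where both the intervention and control group consist of grandparent-grandchildren pairs". It adds: "Restricted randomization will be performed by stratifying gender, initial closeness level of the grandchildren, and age group of the grandparents". Participants gives the numbers: "The aim is to recruit 60 grandparent-grandchild pairs, which will be split evenly into intervention and control conditions". Entry is open-ended; Recruitment says: "We will recruit study participants and make visits until we have 60 pairs that meet the inclusion criteria and agree to participate".

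Alternative Study Designs, placed under Results after the pilot lessons, raises two worries. The first is that volunteers probably join in order to receive the posts; the proposal there is a crossover, so that everyone eventually does. The second is slow recruitment. The trigger reads "In case the researchers are unable to randomize 60 pairs of participants at the same time due to low rate of recruitment", and the proposal is that "a quasiexperimental design would provide flexibility in choosing the control group, allowing those who agree to participate in the study to experience the intervention". The section acknowledges possible selection bias in one sentence and says that any such change would be made by amendment.

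Limitations returns to the subject: "unsuccessful recruitment of study participants, which led us to reconsider the study design, can be a limiting factor". Pilot reports that 59 pairs were recruited and that data collection ended in November 2019.

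**The concern.** The trigger treats simultaneous randomisation of all 60 pairs as a condition for randomising at all. If that premise is wrong, the alternative gives up the main protection of the design for no gain.

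What it puts in place of randomisation is unfavourable. The same section expects volunteers to be drawn by the intervention itself. Placing them in the intervention arm, and finding controls elsewhere, makes arm depend on motivation. The outcomes are the grandchild's own ratings of closeness, investment and conversational resources, which motivation could plausibly move over two months. RQ1 to RQ3 ask whether sharing pictures and stories increases these outcomes, and a comparison built this way could not separate the sharing from the kind of person who wanted it.

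**Working it through.** **1. Does any step need a common start?** Taking the sections in turn:

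- Recruitment: pairs are added until 60 are reached; eligibility is confirmed by a phone interview with each grandparent.
- Home Visit: by individual appointment.
- Premeasurement: a scheduled meeting with the grandchildren; no common date is fixed.
- Intervention: a separate closed Facebook group for each grandchild, one post a week.
- Postmeasurement: an individual meeting after two months.

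No step is delivered to a group or tied to a shared date. Allocation can therefore be made pair by pair.

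**2. Does sequential allocation keep the arms balanced?** The protocol names three stratification factors but not their levels, so I assume two each: 2 × 2 × 2 = 8 strata. Simulating 60 pairs arriving one at a time (5,000 runs), the absolute difference in arm size was:

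| Block size | Mean | 95th percentile |
|---|---|---|
| 2 | 1.5 pairs | 4 pairs |
| 4 | 2.0 pairs | 4 pairs |

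**3. Does the planned analysis remove the bias?** Statistical Analysis specifies ANOVA with group and time. With two time points, the interaction compares mean change between arms:

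expected contrast = effect of sharing + (trend in the intervention arm without sharing − trend in the control arm without sharing).

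A stable baseline difference cancels. The bracket does not. It is zero in expectation under randomisation, but not when motivation decides the arm.

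**4. How large could it be?** The protocol gives no SD, effect size, alpha or power, so there is no stated figure to reproduce and every input except 30 per arm is assumed. Take no true effect, a spurious difference in change of δ SD and a two-sided 5% t-test. The noncentrality is δ × √(30/2) = 3.873δ, on 58 degrees of freedom.

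| δ (assumed) | 3.873δ | Rejection probability |
|---|---|---|
| 0 (randomised) | 0 | 5% |
| 0.3 | 1.16 | 20.8% |
| 0.5 | 1.94 | 47.8% |

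A simulation (20,000 runs per setting) built δ up from an unmeasured motivation factor: δ = r × gap, where r is its correlation with the outcome and gap is the between-arm difference in motivation.

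| r | gap (SD) | Bias (SD) | False positives, self-selected | False positives, randomised |
|---|---|---|---|---|
| 0.2 | 0.5 | 0.10 | 7.0% | 5.1% |
| 0.3 | 1.0 | 0.30 | 21.0% | 4.9% |
| 0.5 | 1.0 | 0.50 | 47.5% | 5.2% |

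For scale, 30 per arm has 80% power only at about 0.72 SD (normal approximation), so biases at the upper end approach the effects that the trial could detect.

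**5. What does a shortfall cost instead?** The standard error of a difference in means scales with √(1/n₁ + 1/n₂). For 59 pairs split 30 and 29, relative to 60, it is √[(1/30 + 1/29) ÷ (2/30)] = √1.017 = 1.009, or 0.9% wider. For 40 pairs split evenly it is √(60/40) = 1.22, or 22% wider. That loss is visible in the confidence interval; selection bias is not.

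**The case against.** The strongest reply is that this is not the plan. The trial is specified as a stratified 1:1 RCT, and the Summary and Conclusion repeat this. The alternative is conditional, depends on an amendment, and comes with its own bias warning; an amendment could still set rules for choosing and adjusting for controls. All of that stands. The point is that the bias is avoidable and left without a remedy, not that it is concealed.

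A reader might infer from Limitations that randomisation was in fact abandoned, or was about to be. The document does not support that. The reconsideration mentioned there may mean no more than the alternatives already listed, and 59 of the intended 60 pairs were recruited. Equally, 59 recruited pairs do not prove that randomisation was kept.

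It is also fair to say that the 21% and 48% are ordinary t-test power with the effect relabelled as bias. They show what assumed differences would do; they are not estimates for this trial. Self-report by unblinded grandchildren affects the randomised design too and is no separate argument against the alternative.

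Finally, randomising after premeasurement is not merely a change of wording. The text places the picture-collecting home visit before premeasurement, while Study Design and Intervention say that controls have no picture collection. The order of steps has to be restated.

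**Conclusion.** The point holds as a criticism of a disclosed, conditional alternative, not of the operative design. Being unable to randomise 60 pairs together is no reason to stop randomising, since every step is arranged per pair. The alternative would link allocation to motivation, and the group-by-time interaction would carry any resulting difference in trend.

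The size of the bias is unknown. Under assumed differences in change of 0.3 to 0.5 SD, 30 per arm and a two-sided 5% test, the false-positive rate would be about 21% to 48%, against 5% under randomisation; with a weaker assumed link it falls to about 7%. The conclusion about design logic does not depend on these figures.

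Sequential randomisation solves staggered entry, not a final shortfall. Dropping randomisation does not itself create eligible pairs either, although it might make joining more attractive.

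**What to change.** 1. Replace the quasi-experimental alternative with sequential stratified randomisation: small permuted blocks within strata, or minimisation on the three named factors. Time posting and postmeasurement from each pair's own start.
2. Obtain the grandchild's initial closeness before allocation, because it is a stratification factor. Restate the order of steps so that picture collection follows allocation and takes place in the intervention arm only. The grandparent's consent, now taken at the home visit, then needs its own place before allocation.
3. If fewer than 60 pairs are reached, keep the design and report the wider confidence interval.
4. Meet volunteers' wish to receive the posts through the protocol's own crossover proposal or a delayed start for controls after postmeasurement. Both keep the randomised comparison of the first two months.
5. Because data collection is complete, report how the 59 pairs were actually allocated. If the alternative was used, limit the conclusions on RQ1 to RQ3 to association.

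The cost is an allocation list, revised text and a reordered home visit; no extra pairs are needed. The drawback is that some willing participants are first allocated to control. For this trial only item 5 can still be acted on; the others serve later use of the protocol.

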## Discussion

### Summary

This protocol presents the design of an RCT to assess effects of sharing old pictures with grandchildren on intergenerational relationships with further recommendations to execute the protocol in future studies.

### Strengths

Maintaining intergenerational relationship over time is beneficial to both young and older adults. However, very few interventions focus on the specific challenges of intergenerational interactions, especially from the young adult side. This study proposes an intervention to maintain and improve the relational quality in the grandparent-grandchild relationship using social media. Social media are widely used among the youth and are therefore a promising resource to discover interesting aspects of the life of their loved ones, which could potentially translate in more conversational resources and motivate an increased commitment in the relationship. Our proposed intervention can be potentially implemented to any society with the technological means, without the need for sophisticated tools.

### Limitations

There are number of possible limitations to this study. First, unsuccessful recruitment of study participants, which led us to reconsider the study design, can be a limiting factor. However, the issue can be attributed to the specific demographical characteristics of Mongolia, as the most sparsely populated country, and other countries may see better chances at successful recruitments. In addition, we proposed an RCT design to identify the impact of social media in the intergenerational relationship instead of a more robust multiple armed RCT design. Although the latter would have been more effective in identifying other factors influencing the intervention, its application would have required a larger population sample, which would have added further challenges to an already complicated recruitment process. Therefore, we opted for collecting qualitative data at the end of the study (debriefing session) to identify additional factors in the intervention, thus mitigating the risks involved in recruiting a larger sample. Furthermore, the study will be carried out only in the city; therefore, people who live in rural areas are not included. Finally, the recruitment will be implemented by reaching out only to the grandchildren; therefore, the future studies will consider involving grandparents in the recruitment in order to reduce the selection bias.

### Conclusion

This paper presented the design of an RCT to assess the effects of sharing old pictures with grandchildren on intergenerational relationships. The intervention leverages the practice of reminiscence and social media sharing to empower grandchildren through the sharing of family stories. We focused on grandchildren, and particularly young adults, as changing their communication behavior and investment can have great effects on the relationship with their grandparents. The proposed intervention can be potentially implemented in any society with the technological means, without the need for sophisticated tools. The results from the pretest pilot highlight some practical recommendations for deploying the protocol.

## Appendix

Multimedia Appendix 1 Project evaluation by the funding agency (European Commission). The project evaluation is based on the activities planned, including user studies.

## Abbreviations

ANOVA: analysis of variance
FCQ: Friendship Chemistry Questionnaire
IMS: Investment Model Scale
IOS: Inclusion of Other in the Self scale
NRI-RQV: Network of Relationships Inventory–Relationship Quality Version
RCT: randomized controlled trial
RQ1: research question 1
RQ2: research question 2
RQ3: research question 3
